| Interventions and Treatments | 
Investigational Medicinal Product (IMP): mTOR inhibitor sirolimus
Trade name: Rapamune®
 
Pal formulation: 1 mg/ml oral solution
Routes of administration: oral
 
Dosage: Sirolimus will be administered as oral solution adapted to body surface area with a starting dose of 0.5 mg/m^2/day (<1 months of age) to 0.9 mg/m^2/day (3- <4 months of age) divided BID (twice daily) until 2 years of age. Sirolimus 12h trough levels will be measured at every study visit and doses titrated and adapted to reach target trough levels of 5-10 ng/ml.
 
Control intervention: standard of care (SOC)
 
Treatment duration: starting within the first 4 months of life and continued until the 2nd birthday.
 |
| Ethical Considerations       | 
Reducing neuropsychologic deficits will improve quality of life and participation, as well as reduce morbidity and mortality, hospitalization, socio-economic costs, and the number of pharmacologic and non-pharmacologic therapies required for the treatment of associated long-term complications.
                                                                                                                                                                                                                                                                                                                                                                                                                                                                        |
| Number of Sites              | 17-20                                                                                                                                                                                                                                                                                                                                                                                                                                                                                                                                                                                                                                                                                                                                                                                |

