### 1.3.8 Long-term tolerability of sirolimus in neonates and young infants

Information on the tolerability and long-term effects of sirolimus on growth, development, and maturation of relevant organ systems in this young age group is limited. Maria *et al.* presented data of a 5-year follow-up study of 22 children with hyperinsulinemic hypoglycaemia (CHI) with a median age at start of sirolimus treatment of 3.87 months and a median starting dose of 0.96 mg/m^2/d [46]. Side effects of treatment occurred in 86.4% with a median delay of 13 months (range 1-52). Infections were most commonly reported (17/22). No growth disturbances or failure to thrive were observed. A review of the off-label use of sirolimus and everolimus in 101 published reports of diverse indications, including 255 children with TSC treated with sirolimus at a median dose of 3.6 mg/m^2/d, did not report relevant long-term use complications of treatment [44]. The experience with sirolimus in kidney transplant patients shows a good overall safety profile and was associated with a lower risk of developing malignancies compared to other immunosuppressants [47]. A retrospective, multicenter chart review of severe adverse events (SAE) associated to sirolimus “off-label” therapy for vascular anomalies identified 17 SAEs in 14 patients. The age at initiation of sirolimus therapy was under 2 years (n = 5), 2–6 years (n = 5), and older than 12 years (n = 4). SAEs occurred during the first 3 months of therapy (n = 7), between 3 and 12 months (n = 7) and after 1 year of therapy (n = 3). The most frequent SAE was viral pneumonia (n = 8) resulting in one death due to a metapneumovirus infection in a 3-month-old child and a generalized adenovirus infection in a 28-month-old child. Sirolimus blood level at the time of SAEs ranged between 2.7 and 21 ng/L [32]. In a study of pediatric liver transplant recipients (n=50) under therapy with everolimus in combination with reduced tacrolimus or cyclosporine A, most male patients (87.5%) had testosterone levels below normal range. This was not associated to changes in height or weight percentiles. Among patients available for Tanner staging after 12 months of therapy, all patients aged <8 years belonged to Tanner stages 1 or 2. No events of abnormal sexual maturation were reported during the study period. Although limited by sample size, these findings indicate that combination of mTOR inhibitors such as everolimus with tacrolimus or cyclosporine A does not appear to negatively impact linear growth or sexual maturation in pediatric liver transplant recipients up to 12 months post treatment initiation [48]. Other clinical data on potential adverse effects on longitudinal growth in renal transplant recipients is inconclusive [49, 50], and information on the effects of low-dose treatments with sirolimus on organ development and growth is lacking. Given the lack of data, we additionally assessed available information from

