### 5.2.2.7 Excipients with known effect

The IMP Rapamune® contains up to 25 mg ethanol and 350 mg propylene glycol (PG; E1520) per ml. In infants and neonates, both excipients are known to have potential adverse effects in case of intoxication such as hypoglycemia, acidosis, tachycardia, hypothermia, hyporesponsiveness, and disorders of consciousness (ethanol) as well as CNS toxicity, hyperosmolarity, hemolysis, cardiac arrhythmia, seizures, agitation, and lactic acidosis (PG) [62, 63]. Given the male 50th percentile, neonates will be exposed to approximately 0.8 mg/kg/d ethanol and 11 mg/kg/d PG following the herein depicted dosing scheme. Both substances are frequently found in oral applications of drugs used in neonatological and pediatric units but have to be critically applied in neonates regarding the reduced capacity of the two predominantly metabolizing enzymes, especially alcohol dehydrogenase, and catalase [63-66]. In case of ethanol, the European Medicines Agency (EMA) states the lacking information on the effects on long-term exposure to low levels of ethanol on child health and development (EMA/CHMP/43486/2018 Corr.1). *Pandya et al.* conducted a study in preterm infants, in which blood ethanol levels of 49 neonates were measured under treatment with drugs containing ethanol as an excipient [64]. On average, the exposure was 1.1-11.8 mg ethanol/kg/d, up to 15-fold daily amounts compared to the regimen of this study, that did not result in significantly elevated blood ethanol levels compared to neonates without any medication. Of note, ethanol-exposed neonates showed elevated concentrations of the toxic ethanol metabolite acetaldehyde, with yet unknown clinical significance. The authors concluded that drugs with 0.3–7.5% ethanol content do not result in toxicologically relevant systemic blood concentrations of ethanol of preterm infants, compared to 3 vol% ethanol content of the IMP [64]. In this study, neonates will be approximately exposed to 11 mg/kg/d PG by IMP application. Due to studies showing low body clearance of PG in this age group and further potential sources of PG on neonatology units [66-69], the EMA sets the safety limit to 1 mg/kg/d (EMA/175205/2014). Furthermore, the co-administration of ethanol and PG might lead to additive effects as both substances are metabolized by the same enzyme, alcohol dehydrogenase [63]. In contrast, in the first weeks of life, an increasing metabolism of both excipients, as a continuum, can be expected regarding age-dependent alcohol dehydrogenase enzyme capacities [65, 70]. In case of PG, this is reflected by extension of the reference value to 50 mg/kg/d in children >1 month of age (EMA/CHMP/704195/2013) [71, 72]. Due to the IMP formulation, ethanol and PG exposures are not avoidable within the scope of this study, also for infants <4 weeks of age. Although this vulnerable age group will likely represent only a small fraction of probands, it is nevertheless expected to benefit in particular as early treatment is likely crucial for neuropsychological outcome. For risk minimization, several measures will therefore be taken: 1.) Excipient exposure is minimized by a low-dose regimen that includes dose fractioning to twice daily to avoid toxic peak concentrations. In the neonatal period, dose fractioning will be maintained for daily volumes <0.2ml to address the reduced excipient metabolism in this age group. For infants ≥4 weeks, minimal single volumes of 0.1ml will be applied. If necessary, switching to a once-daily regimen is allowed, given the improved excipient metabolism with a 50-fold higher safety limit of PG exposure. 2.) Caregivers are sensitized to elimination of further ethanol and PG sources wherever possible. This includes concomitant medications such as phenobarbital, lorazepam, phenytoine, and further drugs [63, 73]. 3.) Neonates will receive a close risk monitoring for accumulation and systemic toxicity with additional visits. Caregivers of the neonates who receive their first dose of IMP under the age of 4 weeks (corrected gestational age <4 weeks of life) will have up to two additional telephone calls by the study personnel up to the end of the 4th week of life. These calls will take place in those weeks (+/-2 days) where no titration visit takes place. Telephone calls instead of onsite-visits will be performed to reduce stress to the neonates wherever possible. Subinvestigators and caregivers will be sensitized to the above stated clinical signs of intoxication and neurologic, cardiovascular, and respiratory status will be conducted at any visit. Caregivers will be advised to report any clinical signs suspicious for intoxication to the study personnel whenever they occur. If any signs occur that require an on-site

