#### 5.5.2 Maximum dose allowed

After the study drug has been started at the doses listed in, subsequent dosing will be individually adjusted informed by measurements of trough levels carried out at each study visit to reach target trough levels of 5-10 ng/ml.

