#### 5.5.3 Dose modifications and interruptions

Two clinical trials in the United States (ClinicalTrials.gov: NCT05104983) and Poland (ClinicalTrials.gov: NCT04987463) are currently evaluating whether infantile-onset sirolimus

treatment can prevent/delay seizure onset in TSC. The following scheme for dose adjustments was established in collaboration with the study teams of the currently active trials in the US and Poland and is informed by previous experience in the use of sirolimus in this age group. No relevant AEs or overdosing occurred in the above-mentioned studies to date (as of 12/2022). Along these lines, in a previous study of patients with TSC-related seizures (EXIST-3 study), the investigators report that even twofold increases of normal everolimus blood levels did not significantly increase the risk of stomatitis or infections [92].

Table 5: Sirolimus dose adjustment

| Sirolimus trough levels (PK in ng/ml) | Required dose adjustment                                                                                                                    |
|---------------------------------------|---------------------------------------------------------------------------------------------------------------------------------------------|
| PK < 5                      | double all subsequent doses; additional telephone contact of trial site with caregiver(s) after 7 days +/- 2 days; repeat levels in 2 weeks |
| 5 ≤ PK ≤ 10                    | no adjustment                                                                                                                               |
| 10 < PK ≤ 15                | if no clinically significant AE or laboratory abnormalities occur, no dose adjustments; repeat levels in 2 weeks                            |
| 15 < PK ≤ 20                | reduce all subsequent doses to 75%; repeat levels in 2 weeks                                                                                |
| PK > 20                     | skip next dose, then reduce all subsequent doses to 50%; repeat levels in 2 weeks                                                           |

Legal guardian(s) should be informed by telephone or e-mail of dose adjustment by trial site as soon as laboratory results are available at trial site. Legal guardian(s) should be advised to contact the trial site if they did not receive a phone call or e-mail within 4 days after the last study visit.

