## 6.4 Safety Lab Visits

Neonates who receive their first dose of IMP under the age of 4 weeks (corrected gestational age <4 weeks of life): Caregivers will have up to two additional telephone calls by the study personnel up to the end of the 4th week of life. These calls will take place in those weeks (+/-2 days) where no titration visit takes place. Caregivers will be asked about the condition of their child. If it turns out that any sign occurs that requires an on-site visit, the study staff will act accordingly. At the discretion of the investigator, a blood sample could be taken for a safety laboratory. On the day of this onsite-visit, IMP should be given to the child corresponding to the Treatment Visits (see also chapter 5.4). Visits could be on the same day as Titration Visits.

If a blood sample for a safety will be collected (collection of max. 1-2 ml blood), following parameters should be analyzed:

|                                                                    |                                              |                                |
|--------------------------------------------------------------------|----------------------------------------------|--------------------------------|
| Clinical Trial Code: PROTECT
EU trial number: 2022-502332-39-00 | Trial Protocol
(Version 06; (01.10.2024)) | Page 70 of 110
CONFIDENTIAL |
|--------------------------------------------------------------------|----------------------------------------------|--------------------------------|

- Blood alcohol concentration (BAC)
- Surrogate parameters for potential propylene glycol (PG) intoxication: electrolytes, osmolality, creatinine, urea, pH, lactate, bicarbonate, anion gap, and the calculated osmol gap

Telephone calls instead of onsite-visits will be performed to reduce stress to the neonates wherever possible.

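### The neonatal propylene glycol and ethanol exposures in 5.2.2.7 hold only at the undoubled starting dose; the unlimited doubling in Table 5 can take propylene glycol past the protocol's own 50 mg/kg/d reference, and no step calculates it.

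*Protocol*

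**What the plan says.** Section 5.2.2.7 states that the product "contains up to 25 mg ethanol and 350 mg propylene glycol (PG; E1520) per ml" and that "neonates will be exposed to approximately 0.8 mg/kg/d ethanol and 11 mg/kg/d PG following the herein depicted dosing scheme". It sets the PG figure against a neonatal limit of 1 mg/kg/d, which it openly exceeds, and then cites the "extension of the reference value to 50 mg/kg/d in children >1 month of age". That higher value supports allowing once-daily dosing from 4 weeks. For ethanol, it compares the trial with a cited preterm study in which exposure was 1.1–11.8 mg/kg/d, and describes this as up to 15 times the trial's daily amount.

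Table 4 (section 5.5) sets starting doses of 0.5, 0.6, 0.74 and 0.9 mg/m²/day for the four monthly age bands from birth to under 4 months. For a trough below 5 ng/ml, Table 5 (section 5.5.3) requires the site to "double all subsequent doses", with a call at 7 days and a repeat level at 2 weeks. It does not limit the number of doublings. Section 5.5.2, titled as the maximum dose, says only that "subsequent dosing will be individually adjusted informed by measurements of trough levels".

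Up to two extra telephone calls are planned for infants first dosed before 4 weeks, ending with the fourth week of life. Section 6.4 adds: "At the discretion of the investigator, a blood sample could be taken for a safety laboratory". Its panel is blood alcohol plus surrogates for PG intoxication.

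**The concern.** The exposure figure is offered as the consequence of the dosing scheme, but it describes only the first dose of one age band. Three arguments in 5.2.2.7 rest on it or on the 50 mg/kg/d reference: the low-dose justification, the ethanol comparison, and the relaxation from 4 weeks of age. No calculation in the protocol shows that exposure stays below 50 mg/kg/d once Table 5 has been applied.

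An ethics committee or the DSMB reading this section sees an exposure that titration may multiply by two, four or more. Several PG effects named there, such as seizures and CNS toxicity, overlap with manifestations of tuberous sclerosis, so clinical observation alone discriminates poorly. Hypoglycaemia is the first ethanol effect named, yet blood glucose is in neither the safety panel (6.4; 6.8, safety laboratory analyses) nor the chemistry list (6.8). Glucose appears only on the urine dipstick.

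**Working it through.** **Inputs from the protocol.** Product strength is "1 mg/ml oral solution", so each mg of sirolimus carries 350 mg PG and 25 mg ethanol. Starting doses are from Table 4. Body surface area (5.5) is BSA = 0.0235 × height^0.42246 × weight^0.51456. Titration visits are 14 days apart (Table 1).

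**Assumed inputs.** Section 5.2.2.7 refers to the male 50th percentile without giving sizes. Assumed: birth 49.9 cm/3.35 kg; 2 weeks 52.5/3.9; just under 1 month 54.5/4.4; 1 month 54.7/4.5; 2 months 58.4/5.6; 3 months 61.4/6.4; 6 months 67.6/7.9; 12 months 75.7/9.6; 24 months 87/12.2.

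**Formula.** PG (mg/kg/d) = dose (mg/m²/d) × BSA × 350 / weight. For ethanol, replace 350 by 25.

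**Reproducing the stated figures.** At birth, BSA = 0.228 m² and the dose is 0.5 × 0.228 = 0.114 mg/d. PG = 0.114 × 350 / 3.35 = 11.9 and ethanol = 0.85. At 2 weeks the results are 11.3 and 0.81; just under 1 month, 10.8 and 0.77. This matches the stated 11 and 0.8, with no doubling.

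**Applying Table 5.** The lower value in each range holds the doubled mg dose fixed while weight rises at each 14-day step (assumed: birth start 3.35, 3.8, 4.4, 5.0 kg; 1 month 4.5, 5.0, 5.5, 6.0; 2 months 5.6, 6.0, 6.4, 6.7; 3 months 6.4, 6.7, 7.0, 7.3). The upper value holds size constant.

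| Start | No doubling | One | Two | Three |
|---|---|---|---|---|
| Birth | 11.9 | 21.0–23.9 | 36.3–47.7 | 63.9–95.4 |
| 1 month | 12.9 | 23.2–25.8 | 42.2–51.6 | 77.4–103 |
| 2 months | 14.7 | 27.4–29.4 | 51.5–58.8 | 98.3–118 |
| 3 months | 17.1 | 32.7–34.2 | 62.6–68.5 | 120–137 |

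Values are mg/kg/d PG. A slightly smaller 3-month infant (62 cm, 6.2 kg) starts at 17.5, so two doublings at constant size give 17.5 × 4 = 70.

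**Neonatal period.** An infant started at birth and doubled at V2 (day 14) receives 0.114 × 2 × 350 = about 80 mg PG per day. That is 80/3.35 = 23.9 mg/kg/d with no weight gain, 21.0 at 3.8 kg and 20.5 at 3.9 kg.

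**Ethanol margin.** The protocol's 15-fold is 11.8/0.8 = 14.75. After that doubling, ethanol is 0.114 × 2 × 25 / 3.8 = 1.5 mg/kg/d and the margin is 11.8/1.5 = 7.9 (1.7 and about 7-fold with no weight gain). Exposure is then inside the cited study's 1.1–11.8 range, in which raised acetaldehyde of unknown clinical significance was reported.

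**Dose equivalent to the reference.** 50/350 = 0.143 mg/kg/d sirolimus, or about 2.3–2.6 mg/m²/d at 1–3 months and 2.8–3.1 at 6–24 months. Section 1.3.8 cites a review "including 255 children with TSC treated with sirolimus at a median dose of 3.6" mg/m²/d; at 6–24 months that would be 50 × 3.6/3.10 = 58 to 50 × 3.6/2.80 = 64 mg/kg/d. The ages of those children are not given, so this is indicative only.

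**What repeated doubling requires.** If troughs are proportional to dose and clearance is constant, a second doubling needs an initial trough below 5/2 = 2.5 ng/ml, and a third below 5/4 = 1.25.

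**The case against.** Much of the counter-case stands. One doubling never reaches 50 mg/kg/d in these calculations. Going past it takes consecutive low troughs, whose frequency the documents do not give; section 6.8 expects every patient to reach target during titration. Section 5.5 describes 0.05–0.1 mg/kg as in line with its scheme, which gives 17.5–35 mg/kg/d PG, below the reference. Still, section 5.5 reports clearance rising with age, and a cohort in 1.3.7.1 with a lower target had levels down to 0.79 ng/ml, so repeated doubling is plausible.

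A reader might infer that two doublings take every start from 1 month above 50. They do not: with weight gain the 1-month start is about 42.

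A reader might also infer that nothing is checked after week 4. The documents do not support that either. Clinical status is assessed at every visit, and caregivers are asked to report signs of intoxication whenever they occur. Each doubling brings a call and a repeat trough, and further laboratory tests may be ordered at any time (6.8). The DSMB meets after five treated patients complete titration (12.5.1), and individual risk-benefit reviews follow at 6, 12 and 18 months (1.3.10). Since 5.2.2.7 names seizures as a PG effect and alerts staff to it, one cannot claim that toxicity would go unrecognised.

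What this leaves untouched is that none of these steps calculates PG or ethanol exposure. The extra calls and the discretionary panel are described operationally only up to the fourth week.

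**Conclusion.** The point holds in a limited form. The 11 and 0.8 mg/kg/d figures are starting-dose values for the youngest band and do not bound exposure under the scheme, even in neonates. Starts at 1, 2 and 3 months already give about 13, 15 and 17 mg/kg/d PG. One doubling in the neonatal period gives about 20–24. PG can pass 50 mg/kg/d after two doublings for starts at 2–<4 months (about 52–70), and after two or three for earlier starts.

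The sizes are assumed medians, so individual values will differ. The finding is that exposure can exceed the reference, not that it will, and no frequency can be derived from the protocol. It shows neither that toxicity would occur nor that monitoring stops. It shows that a safety figure on which the excipient argument relies is understated, and that sections 5.2.2.7, 5.5.2 and 5.5.3 do not fit together.

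**What to change.** 1. In 5.2.2.7, replace the single figures with a range of PG and ethanol in mg/kg/d by starting age and number of Table 5 doublings, stating the body sizes used. Correct the 15-fold ethanol comparison accordingly.
2. Reconcile 5.2.2.7 with 5.5.2 and Table 5, so that the exposure assessed is the exposure the scheme can produce.
3. Reconcile 6.4 and 6.8 with 5.2.2.7 on when the excipient panel applies and whether it covers the effects named, including hypoglycaemia.
4. Have the eCRF, which already holds dose and weight, display PG and ethanol in mg/kg/d at each dose change, so that investigators and the DSMB see actual exposure.

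No dose, limit or laboratory trigger is proposed; those are for the sponsor. For example, a trigger at 11 mg/kg/d would flag a median newborn at the undoubled starting dose (11.9). The cost is one eCRF calculation, revised text and a less favourable stated figure. None of these four changes in itself requires an extra visit or blood sample.

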### 5.2.3 IMP Supplies

The IMP will be provided free of charge by Pfizer to the pharmacy of the University Hospital Heidelberg (central pharmacy). The appropriate number of drug bottles will be dispensed to the sites by the central pharmacy.

The trial site will be equipped with one drug bottle Rapamune® by the pharmacy of the University Hospital Heidelberg for the first scheduled screening visit.

Re-supplies of the IMP have to be obtained by sending an order form to the central pharmacy. The required amount of investigational medicinal product will be shipped to the study sites by the pharmacy.

The trial centres have to keep records of the trial medication on a patient-specific drug accountability log and a site-specific inventory log on receipt, distribution, use, return, loss, or other disposition of medication in alignment to the receipts of drug shipment. Above-mentioned logs will be approved and provided by the sponsor. The documents contain information about dates, quantities, batches or code / serial numbers and patient identification codes.

At each study visit the caregivers have to return the used bottles. At the trial site, a responsible member of the study team will assess the returned amount of study medication by measuring the filling level of the used medication bottle using a scale with a quantity indication in ml provided by the sponsor.

Trial medication that may no longer be used (e.g. excess temperature, expired) may be destroyed before the end of trial after verified and released by the monitor. At the end of the trial, all unused and expired trial medication has to be destroyed at trial site. This must be documented on the respective logs. If the destruction at trial site is not possible, the medication can be sent to the sponsor for destruction. The trial site will receive a report for the ISF.

